We expect that any effects before 14 days for first dose vaccination will reflect programmatic effects (e.g. being instructed not to attend vaccination if symptomatic and reinforcement of behavioural advice to reduce COVID-19 related risks). Follow up will therefore start from day 14 after the date of first dose vaccination (and day 7 after second dose) for both the exposed and control person. It will end for both the exposed and control person on the first of: experiencing the outcome of interest, death (from any cause) or end of follow up period. Unvaccinated controls who become vaccinated will be eligible to become considered as exposed, after follow up is censored for the exposed-unexposed pair at the date of vaccination of the control. Follow-up of the exposure period will also be censored for both the recipient and the control if the partially vaccinated recipient participant received a second dose. Analyses will be stratified by vaccine type.

For the matched cohort analysis, we will draw Kaplan Meier curves to inspect cumulative incidence. We will then fit Poisson regression models to estimate rate ratios (RRs) with 95% confidence intervals (95% CIs) for the association between exposure group and risk of the outcomes, at weekly time periods from exposure to event (Section 4.2).

We will fit a model including a spline with person-time defined in days, to explore the timing of any waning of vaccine effectiveness. The splines will be fit using thin plate regression splines (the R package ‘mgcv’ default settings) with weekly knots from days 14 to the maximum week. The difference between the smooths in the exposure groups will be calculated using methods by Simpson, [7] to obtain smoothed estimated RRs between the exposure groups at daily follow-up periods.

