We will assess vaccine waning using two different pre-specified approaches: first, conducting statistical hypothesis tests for declining effectiveness; and second, by assessing whether effectiveness is maintained above a minimum acceptable level. For the former, we will assess the curvature of the association in the spline modelled estimates over time, to evaluate whether the smoothed estimates peak and return to null. This will be achieved by fitting the same statistical model as for the spline but replacing the spline term with a quadratic term and post 14 days only. A statistically significant positive quadratic coefficient from this model in the exposed group would suggest waning. For the latter approach, we adopted the US Food & Drug Administration’s threshold of achieving a RR of at least 0.5 for the point estimate. [8]

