### 5.5.3 Cohort analysis

Given the relatively small number of anticipated COVID-19 deaths during the follow up period, the secondary analysis focusing on mortality will be based on data from the whole cohort. In addition, secondary analyses will be conducted for COVID-19 hospitalisation.

Vaccination status (unvaccinated and one dose) will be defined as a time-varying exposure. Poisson regression adjusted for an offset representing the time at risk, with rate ratios (RRs) and 95% confidence intervals (CIs) will be calculated. Vaccine effectiveness and 95% Confidence Intervals (CIs) will be calculated as (1-Rate Ratio)*100. Models will be adjusted for relevant confounders, including age, sex, SES, geography, time period, comorbidities and risk factors. Stratification variables for each week post-vaccination will be included in the Poisson regression. We will assess waning by examining the resulting discrete set of weekly RR estimates. The reason for doing it this way as opposed to including a polynomial/spline in time since vaccination in the Poisson regression is that this would require adding rows to the data for every individual and every time, which would make the dataset impractically large to work with when using the full cohort.

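### The formal waning test in SAP 5.5.2 tests curvature, which is neither necessary nor sufficient for declining effectiveness

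*SAP*

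**What the plan says.** Waning of protection after the first dose is the study's stated aim (SAP 1). SAP 5.5.2 sets out two approaches in the matched cohort. The first is described as "first, conducting statistical hypothesis tests for declining effectiveness". It looks at the curvature of the spline estimates "to evaluate whether the smoothed estimates peak and return to null", and is carried out by "fitting the same statistical model as for the spline but replacing the spline term with a quadratic term and post 14 days only". The decision rule is: "A statistically significant positive quadratic coefficient from this model in the exposed group would suggest waning". The second approach compares the point estimate of the RR with a threshold of 0.5.

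In the parent spline model each exposure group has its own smooth, and the RR comes from the difference between the two. Recipient and control share a time axis: "Follow up will therefore start from day 14 after the date of first dose vaccination". No calendar-time term is named for the matched model. A time-period term appears only in the whole-cohort model of SAP 5.5.3: "Models will be adjusted for relevant confounders, including age, sex, SES, geography, time period, comorbidities and risk factors". There, the plan for waning is: "We will assess waning by examining the resulting discrete set of weekly RR estimates".

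**The concern.** Effectiveness declines when the log RR against matched controls has a positive slope over some later stretch of follow-up. The rule does not ask for that. It requires no rising RR at the end of follow-up, no turning point inside follow-up and, read literally, no contrast with controls. Three things can go wrong:

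- Steady waning has no curvature on the log scale, so the rule cannot see it.
- Protection that builds after day 14 and then holds is convex, so the rule can call it waning.
- If the coefficient is the exposed group's own, it describes a log incidence rate, which carries the shape of the epidemic.

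This is the only formal test of the main question, and it can err in either direction.

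**Working it through.** **Inputs.** The SAP gives no sample size, power or alpha for this test, so there is no design figure to reproduce. I assume 5% two-sided, that is 2.5% in the positive tail, in line with the 95% intervals in SAP 6.1. The filled-in matched table in SAP 5.6.2 gives 1,029 control and 541 vaccinated events from day 14; 541/1,029 = 0.526, which agrees with the printed rates, 2.3/4.4 = 0.523. By vaccine, control events are 488 (BNT162b2) and 541 (ChAdOx1). SAP 4.2 runs the weekly bands to 70+ days, or 77+ if numbers allow. All RR and incidence shapes below are assumptions.

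**Model.** For group g (1 exposed, 0 control), with a log person-time offset: log rate = a_g + b_g·t + c_g·t². Hence log RR(t) = (a₁−a₀) + (b₁−b₀)t + (c₁−c₀)t², and its slope is (b₁−b₀) + 2(c₁−c₀)t. Waning means that this slope is positive. The rule tests c₁ (literal reading) or c₁−c₀ (contrast reading). Neither fixes the sign of the slope.

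**Curvature by hand** (second difference of the log at three equally spaced times):

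- Log-linear waning, RR 0.3 to 0.8, midpoint √(0.3×0.8) = 0.490: −1.204 + 2(0.714) − 0.223 = 0 after rounding. RR rises throughout; curvature is zero.
- Linear loss of effectiveness, RR 0.4, 0.6, 0.8: −0.916 + 2(0.511) − 0.223 = −0.118. RR rises throughout; curvature is negative.
- Build-up then plateau, RR 0.7 at day 14, 0.42 at days 35 and 56: −0.357 + 2(0.868) − 0.868 = +0.511. RR never rises; curvature is positive.
- Constant RR with incidence proportional to 0.12 + 0.88·exp(−5t), t scaled 0 to 1: values 1, 0.192, 0.126 give 0 + 2(1.649) − 2.072 = +1.226 in each group, and zero in the contrast.

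**How often the rule declares waning**, P = Φ(c/SE − 1.96), using daily bins for days 14-77, person-time falling 2% a day, and 1,029 control events unless stated:

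| Assumed truth | Exposed group's own term | Contrast with controls |
|---|---|---|
| Constant RR, flat incidence | 2.5% | 2.5% |
| Log-linear waning, 0.3 to 0.8 | 2.5% | 2.5% |
| Linear loss of effectiveness, RR 0.4 to 0.8 | about 1% | about 1% |
| 0.7 to 0.42 by day 35, then flat | about 57% | 42% |
| Same, 488 control events | about 31% | 23% |
| Constant RR, steep convex fall in incidence (above) | 96% | 2.5% |
| U-shape 0.7 to 0.4 to 0.8, lowest at day 42 | 99% | 91% |

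The first waning row is algebra: three times the events leave it at 2.5%. On the literal reading it also needs control incidence that is flat or log-linear.

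The build-up rows depend on the size assumed. With follow-up to day 76 and person-time halving every 30 days, falls by day 28 give, literal and contrast respectively: 0.8 to 0.45, 76% and 58%; 0.7 to 0.45, 51% and 37%; 0.65 to 0.5, 22% and 16%.

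The epidemic row depends strongly on shape. Replacing exp(−5t) by exp(−3t) gives 28%, and by exp(−2t) 8%. A log-linear fall gives 2.5%, and a hump about 0%.

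**What a slope would do.** An exposure-by-time slope from day 14 has 99.9% power for log-linear waning from 0.3 to 0.8 and 96-97% for 0.4 to 0.8. It misses the U-shape (about 2-3%). Started at day 28, it detects that U-shape in 58-64% of studies if the lowest RR is at day 42, 27-33% at day 49 and 8-10% at day 56, depending on the follow-up assumed. The quadratic contrast has 73-91% over the same cases.

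**The case against.** The best defence is that SAP 5.5.2 names the shape it seeks: effectiveness that peaks and returns to null. For that U-shape the quadratic is a good test. The quadratic model is also described as the spline model with one term replaced, and only an RR can return to null, so the coefficient may well be meant as the exposed-versus-control interaction. Matched pairs share start date and censoring, so on that reading the epidemic cancels. The wording is that the coefficient would suggest waning, and the plan also reports weekly RRs with intervals, daily smoothed RRs and the 0.5 threshold. A day-21 start is listed for consideration in SAP 5.5.6.

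Much of this stands. A reader might infer that the rule cannot detect waning at all; the U-shape results contradict that. A reader might also infer that the epidemic curve is bound to trigger it. The SAP gives no incidence curve, entry is staggered from December to April so that time since dose mixes calendar dates, and the effect needs both a convex curve and the literal wording. Judging waning from weekly RRs with intervals in SAP 5.5.3 is a reasonable secondary analysis, not an error.

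The defence does not reach the other two failures. Missed steady waning and build-up read as waning both survive the contrast reading. The threshold and the weekly RRs can show a large decline but do not test for one. Day 14 is justified in the SAP by programmatic effects, not by completed protection, and the day-21 alternative shows that the start of protection is unsettled. If the quadratic term meant t² with no linear term, steady waning would be found (about 95% for RR 0.4 to 0.8), but the reference to curvature and to a peak points to a full quadratic.

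**Conclusion.** The concern holds in this form: the rule tests curvature, and a significant positive coefficient neither establishes a rising RR nor is needed for one. That it misses log-linear waning is exact on the contrast with controls, and it holds for the exposed group's own curve when incidence is flat or log-linear. False signals from build-up then plateau are real but vary with the assumed size: 42-57% for the main scenario with pooled counts, 23-31% with one vaccine's counts, and 16-22% for a mild build-up. Because analyses are stratified by vaccine type, the lower counts matter; the table appears to be one nation's data (its deprivation index is Scottish), and pooling across the UK would raise both counts and false signals.

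The epidemic-shape problem is an ambiguity of wording that the SAP must resolve, not a demonstrated defect. All rates assume a 5% two-sided test and a quadratic that includes its linear term.

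**What to change.** In SAP 5.5.2:

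1. State that the test is on the exposed-minus-control log RR, through the exposure-by-time interaction, and give alpha and sidedness.
2. Keep the quadratic interaction as a test of shape, and do not declare waning from it alone.
3. Add a directional test of late change in log RR with a 95% interval, from the difference of smooths already planned: for example, the last period against the period of best effectiveness, or against a pre-specified reference period after build-up. If the best period is estimated from the data, allow for that selection.
4. Report with it an exposure-by-time slope from a pre-specified day after build-up. The slope should not simply replace the quadratic, since it is weak when the RR is lowest late in follow-up.
5. Declare waning only when the log RR is shown to rise.

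In SAP 5.5.3, a trend over week number within one-dose time is an optional addition. It uses the weekly categories already in the model, so the plan's objection about extra rows does not apply.

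The cost is SAP wording, a few lines of model code and one more pre-specified test. No new data are needed.

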4.2 Constructed variables

- Time to event in weeks (0-13, 14-20, 21-27, 28-34, 35-41, 42-48, 49-55, 56-62, 63-69 and 70+ days from dose 1, extend to 70-76, 77+ if numbers allow)
- Number of Q Covid risk groups (0,1,2,3,4,5+)
- Number of PCR tests in the pre vaccination era (0,1,2,3-4, 5-9, 10+). This will serve as our proxy for healthcare workers where healthcare worker status is unknown.
- Elderly care home resident (defined as person from a household with more than 10 people and an average age of over 65)

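### The minimum-effectiveness threshold is written the wrong way round, rests on the point estimate alone, and does not name the rate ratio it applies to

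*SAP*

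**What the plan says.** SAP section 5.5.2 gives two pre-specified ways to assess waning in the matched analysis. The first tests the curvature of effectiveness over time. The second works "by assessing whether effectiveness is maintained above a minimum acceptable level", and the level is then fixed as a "threshold of achieving a RR of at least 0.5 for the point estimate", with an FDA guidance document as the source.

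Section 5.5.3 gives the conversion between the two scales: "Vaccine effectiveness and 95% Confidence Intervals (CIs) will be calculated as (1-Rate Ratio)*100".

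The threshold sentence does not say which RR is meant. Section 5.5.2 produces two sets: weekly RRs with 95% confidence intervals from Poisson models, and a spline fit intended "to obtain smoothed estimated RRs between the exposure groups at daily follow-up periods". The periods in section 4.2 are "0-13, 14-20, 21-27, 28-34, 35-41, 42-48, 49-55, 56-62, 63-69 and 70+ days from dose 1", which leaves nine from day 14 onward. For the whole-cohort analysis, section 5.5.3 says "We will assess waning by examining the resulting discrete set of weekly RR estimates", but no threshold is mentioned there. Section 6.1 requires 95% confidence intervals for measures of association. They play no part in the threshold rule.

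**The concern.** Effectiveness falls as the RR rises, so a floor on effectiveness is a cap on the RR. The sentence puts a floor on the RR. Under the literal text, an RR of 0.8 (effectiveness 20%) meets the criterion and an RR of 0.4 (effectiveness 60%) does not.

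This is one of only two pre-specified waning criteria for the primary analysis, and the analysis is run separately in each UK nation before pooling, so the text has to stand on its own. The event counts in the SAP's own table lie close to 0.5, where direction and uncertainty both affect the reading. Because the estimate is not named, two analysts could also apply the same sentence to different quantities and reach different conclusions.

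**Working it through.** **No figure to reproduce.** The SAP gives no power, event target or operating characteristic for this rule, and 0.5 is taken from a cited source. The check is therefore of direction, then of what the SAP's own counts imply.

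**Direction.** VE = (1 − RR) × 100. RR ≥ 0.5 gives VE ≤ 50%. VE ≥ 50% requires RR ≤ 0.5.

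**Inputs.** Events from day 14 onward in the matched-cohort table of section 5.6.2, unvaccinated versus vaccinated: ChAdOx1 541 v 303; BNT162b2 488 v 238; both vaccines 1029 v 541. Matching is 1:1 and pairs are censored together, so person-time is taken as equal and the event ratio stands for the RR. The rounded rates in the table agree: 2.2/4 = 0.55, 2.4/5 = 0.48, 2.3/4.4 = 0.52.

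**Aggregate ratios.** SE(log RR) = √(1/a + 1/b), treating the two counts as independent; 95% CI = RR × exp(±1.96 SE).

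| | RR | SE | 95% CI | VE | Literal rule (RR ≥ 0.5) | Intended rule (RR ≤ 0.5) |
|---|---|---|---|---|---|---|
| ChAdOx1 | 303/541 = 0.560 | 0.072 | 0.487–0.645 | 44.0% | met | not met |
| BNT162b2 | 238/488 = 0.488 | 0.079 | 0.418–0.569 | 51.2% | not met | met |
| Both | 541/1029 = 0.526 | 0.053 | 0.474–0.583 | 47.4% | met | not met |

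Every reading flips with the direction of the inequality, and every interval includes 0.5.

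**Illustration only: if single weekly estimates were used.** Assume the day-14+ control events are spread evenly over nine independent periods (541/9 ≈ 60 for ChAdOx1, 488/9 ≈ 54 for BNT162b2), the true RR is constant, and any period above 0.5 counts as loss of protection. Given n events in a period, vaccinated events follow Binomial(n, RR/(1 + RR)), and the estimate exceeds 0.5 when they exceed n/3. The chance for any of nine periods is 1 − (1 − p)⁹.

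| True RR | ChAdOx1: p per period | ChAdOx1: any of nine | BNT162b2: p per period | BNT162b2: any of nine |
|---|---|---|---|---|
| 0.30 | 0.014 | 0.12 | 0.022 | 0.18 |
| 0.40 | 0.139 | 0.74 | 0.168 | 0.81 |
| 0.45 | 0.278 | 0.95 | 0.311 | 0.97 |

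**Effect of pooling.** The table's deprivation footnote cites the Scottish index, so the counts appear to be one nation's. Section 3.3 gives about 5.3 + 1.4 + 5.4 + 3.1 = 15.2 million people across the UK, against 5.4 million in Scotland. For ChAdOx1 the weekly SE by normal approximation is √(9/303 + 9/541) = 0.215. If events scale with population, it becomes 0.215 × √(5.4/15.2) = 0.128. At a true RR of 0.40, the chance per period falls from P(Z > ln 1.25/0.215) = 15% to P(Z > ln 1.25/0.128) ≈ 4%, and for any of nine from 77% to about 31%. At 0.45 the any-of-nine figure falls from 97% to about 87%.

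**The case against.** The strongest reply is that nobody would be misled. The sentence just before the threshold asks for effectiveness to stay above a minimum, which fixes the intended direction. The study is observational, and no stopping or other action hangs on the rule. This stands as far as intent goes. A reader might infer from the inverted wording that the analysis was run in reverse, but nothing in the SAP shows that. It does not excuse leaving a pre-specified criterion that contradicts its own formula.

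A reader might also infer that the rule is judged week by week and so has a very high false-alarm rate. The SAP does not say so. The threshold is tied to no time unit, the daily smoothed RRs are an equally natural target, and there is no provision that a single period above 0.5 counts as loss. The weekly figures are also sensitive to the assumed true RR and to pooling.

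Finally, the SAP openly adopts an external point-estimate benchmark, and whether that source adds an interval condition cannot be judged from this document. Requiring the upper 95% limit to lie at or below 0.5 would be a materially stricter criterion: at the one-nation weekly SE of 0.215 it needs an estimate of about 0.5/exp(1.96 × 0.215) = 0.33. That requirement is a trade-off, not a correction. What remains is that a point estimate read without its interval is a weak basis for a verdict when both vaccines' aggregate intervals include the cut-off.

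**Conclusion.** The inequality is wrong as written and must be corrected. It contradicts both the purpose stated in the same paragraph and the effectiveness formula in section 5.5.3. At the SAP's own day-14+ counts, the literal and intended rules give opposite readings for each vaccine and for both combined. It is a wording error with a clear intended meaning.

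Two further gaps hold: the rule does not name the RR it applies to, and it ignores uncertainty. The second matters even with all day-14+ events combined, since 0.5 lies inside 0.49 to 0.65 for ChAdOx1 and 0.42 to 0.57 for BNT162b2. These intervals assume equal person-time and independent counts, and they use table counts that appear to come from one nation.

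The weekly noise result is conditional. With one-nation counts it is roughly 75–80% at a constant true RR of 0.40 but only 12–18% at 0.30, and it is lower with UK pooling. It shows why the estimate should be named; it is not a property of the rule as written.

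**What to change.** In section 5.5.2:

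- State the threshold as an RR of at most 0.5, that is, effectiveness of at least 50%.
- Name the estimate and time points it applies to, for example the pooled smoothed curve from day 14 onward, by vaccine type.
- Say that the estimate is read with its 95% confidence interval, and that periods whose interval includes 0.5 are described as not distinguishable from the threshold.

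This takes a few sentences and no new data or models. The cost is that some periods will be reported as inconclusive; on the counts in the table, both vaccines' aggregate day-14+ results would be. If the team prefers to keep a pure point-estimate benchmark, the SAP should label it descriptive.

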### 5.5.3 Cohort analysis

Given the relatively small number of anticipated COVID-19 deaths during the follow up period, the secondary analysis focusing on mortality will be based on data from the whole cohort. In addition, secondary analyses will be conducted for COVID-19 hospitalisation.

Vaccination status (unvaccinated and one dose) will be defined as a time-varying exposure. Poisson regression adjusted for an offset representing the time at risk, with rate ratios (RRs) and 95% confidence intervals (CIs) will be calculated. Vaccine effectiveness and 95% Confidence Intervals (CIs) will be calculated as (1-Rate Ratio)*100. Models will be adjusted for relevant confounders, including age, sex, SES, geography, time period, comorbidities and risk factors. Stratification variables for each week post-vaccination will be included in the Poisson regression. We will assess waning by examining the resulting discrete set of weekly RR estimates. The reason for doing it this way as opposed to including a polynomial/spline in time since vaccination in the Poisson regression is that this would require adding rows to the data for every individual and every time, which would make the dataset impractically large to work with when using the full cohort.

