### 5.5.5 Corrections for multiple testing

N/A

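### Section 5.5.3 judges waning in the whole cohort by inspecting weekly rate ratios with no named contrast or test, and its reason for not fitting a polynomial holds only on a daily time scale

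*SAP*

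**What the plan says.** Section 5.5.3 (Cohort analysis) states that "the secondary analysis focusing on mortality will be based on data from the whole cohort", because few deaths are expected; COVID-19 hospitalisation is analysed there too. On the model it says: "Stratification variables for each week post-vaccination will be included in the Poisson regression". On waning it says: "We will assess waning by examining the resulting discrete set of weekly RR estimates". It explains that a polynomial or spline in time since vaccination was not chosen because "this would require adding rows to the data for every individual and every time, which would make the dataset impractically large" to work with.

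Section 4.2 lists the time bands as "0-13, 14-20, 21-27, 28-34, 35-41, 42-48, 49-55, 56-62, 63-69 and 70+ days from dose 1", with the option to "extend to 70-76, 77+ if numbers allow". Section 5.5.5, headed "Corrections for multiple testing", reads N/A.

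The two pre-specified waning criteria are in Section 5.5.2 (Matched analysis). They are a significance test on a quadratic term that replaces the spline, and a threshold of 0.5 on the RR point estimate. Section 5.5.3 does not carry over either one.

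**The concern.** Effectiveness as a function of time since first dose is the study's first objective (Section 2.2). For death as a single outcome, the sparsest endpoint, the only stated rule is to look at nine or ten noisy estimates. Two analysts, or two nations, could look at the same set and disagree. One chance-high late week could be called waning, and a steady decline spread thinly over the bands could be dismissed as noise. Section 5.5.4 repeats the exercise by vaccine, age group and sex.

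The reason given for stopping at inspection also does not fit the model just described. A Poisson model with a term per week and a time-at-risk offset already needs vaccinated person-time split by week.

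**Working it through.** The SAP gives no alpha, power or error rate for this analysis, so there is no figure of its own to reproduce.

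**1. Number of bands.** Section 4.2 lists 10 bands. Removing days 0-13 leaves 9 from day 14, or 10 if 70+ is split. Section 5.5.3 says only that there is a term per week; I assume the Section 4.2 bands apply.

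**2. What inspection could mean.** Section 6.1 reports 95% CIs, so one directional comparison has a 5%/2 = 2.5% false-positive rate. Weekly deaths are not given. I therefore assume a constant true RR, independent weekly log RRs, and three patterns of precision: equal, events falling 5:1 over the bands, and events rising 1:5. The unvaccinated reference is treated as common to all weeks, so it cancels. The illustrative rule is: waning if, for any later band j,

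z_j = (log RR_j - log RR_1) / sqrt(SE_j² + SE_1²) > 1.96, where band 1 is days 14-20.

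If the eight comparisons were independent, the rate would be 1 - 0.975^8 = 18.3%. They share band 1, so the rate was simulated (400,000 sets, nine bands):

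| Event pattern | Any later band worse than days 14-20 | Ratio to 2.5% |
|---|---|---|
| Equal | 12.4% | 5.0 |
| Falling 5:1 | 14.6% | 5.9 |
| Rising 1:5 | 8.9% | 3.5 |

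With ten bands the range is 9.3% to 15.9%.

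Other reading rules, nine bands:

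| Rule | False-waning rate |
|---|---|
| Last band against first only | 2.5% |
| Non-overlapping 95% CIs | 7.2-7.5% |
| Last band against best earlier band | 8.6-13.5% |
| Any band against the one before | about 19% |
| Any later band against any earlier band | 39-40% |

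The ratio to 2.5% thus runs from 1 to about 16 depending on a rule the plan does not state.

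**3. The row-count reason.** In a test dataset of 100,202 person-week rows, a Poisson model with week indicators had 11 coefficients. Replacing the indicators with a linear week number used the same rows and 4 coefficients. Aggregating to 27 rows (3 covariate groups × 9 weeks) gave the same slope (0.0532) and standard error (0.0129). A quadratic adds one column and no rows. In the plan's model, nine post-day-14 terms would become three: level, slope and curvature.

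**4. Which test to name.** I compared a 1-df linear trend with a 2-df linear-plus-quadratic test. Assumptions: 300 events in vaccinated people in total, and person-time falling linearly to 30% by the last of nine bands.

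| True pattern of RR | 1-df linear trend | 2-df linear + quadratic |
|---|---|---|
| Monotone rise by a factor of 1.5 | 58% power | 48% power |
| Halves by the middle band, then returns | signals waning in 0.2%, strengthening in 26% | detects the time pattern in 93% |

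With no change over time, the two-sided linear test and the 2-df test each reject in about 5% of runs.

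**The case against.** **The error multiple.** A reader might infer that the plan makes false waning five to six times too likely. The documents do not support that. Section 5.5.3 contains no significance rule. The multiple appears only if any later week significantly above days 14-20 counts as waning and weekly events are flat or falling. Even under that rule it can be smaller: a Poisson simulation with person-time rising from 30% to 100% and 100 to 1000 events gave 2.1% to 8.1%. What stands is that the rate is undefined.

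**The row-count reason.** A reader might call it simply wrong. It is not: Section 5.5.2 builds its spline on person-time in days, and on that scale individual-level data would grow as the plan says. It fails only for a week-level term.

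**Sole analysis of death.** This is true only of death as a single outcome. Death is part of the matched composite, and Section 5.5.2 refers to outcomes in the plural.

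**Criteria elsewhere.** The 0.5 threshold in Section 5.5.2 could be applied to weekly RRs. But Section 5.5.3 does not say so, and the threshold concerns a minimum level of effectiveness, not decline. The quadratic test is tied to a model that Section 5.5.3 declines to fit.

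**A linear trend could mislead.** This objection stands. Section 5.5.2 looks for estimates that peak and return to null. Against such a pattern a linear trend can point the wrong way (step 4), so the repair needs curvature.

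**Limited stakes.** This is a secondary analysis reported with confidence intervals; the formal test belongs to the primary matched analysis. That limits the severity but supplies no rule for the mortality result.

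**Conclusion.** The point holds in this form. Section 5.5.3 fixes no way of deciding waning in the whole cohort, so its false-waning rate cannot be stated. The 9-15% against 2.5% is an illustration. It rests on one supplied rule, nine bands, independent weekly log RRs and the three assumed event patterns. The row-count reason does not exclude a polynomial in week number, which the planned data already support. This should be corrected: the analysis is secondary, but it carries the mortality result, and the correction is close to free.

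**What to change.** In Section 5.5.3:

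- **Test.** Add a pre-named test of change in log RR over the post-day-14 bands. Enter linear and quadratic week-number terms for vaccinated person-time in the same week-split Poisson model and test them jointly on 2 df at a stated alpha. Equivalently, fit the same curve by generalised least squares to the weekly log RRs with their covariance matrix.
- **Open band.** State the score for 70+, for example its mean follow-up time. With the study running from 8 December to 30 April, that band can span days 70 to 143.
- **Reporting.** Give both coefficients and the fitted late-versus-early ratio of RRs with 95% CI, and pool them across nations. The joint test detects change in either direction, so direction is read from these. The coefficients are needed because a fall followed by an equal return leaves the late-versus-early ratio near 1.
- **Display.** Keep the weekly RRs as the display.
- **Row-count sentence.** Limit it to a daily-scale spline.

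The cost is a change of wording and one extra fit on the existing dataset. The downside is some loss of power against a 1-df trend when waning is monotone (48% against 58% in the example above).
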